#### Other sociodemographic and clinical measures

Measures of demographic, hearing and characteristics of the intervention and control groups will be collected at T0, which include: gender, Australian residency, eligibility for governmental assistance in hearing, Aboriginal or Torres Strait Islander status, Australian state or territory residence, annual household income, employment status, educational status, marital status, duration of hearing difficulty and subjective level of hearing ability, hearing test(s) previously conducted, digital literacy, English literacy, visual correction/difficulty and other health conditions. Dimensions of the device (eg, smartphone, tablet, laptop) that the participants use will be collected.

### Assignment of interventions

#### Sequence generation

Simple randomisation will be used, with the aim of obtaining a ratio close to 1:1. With large sample sizes, simple randomisation should allow us to reach the same allocation as other, more complex methods, such as block randomisation. Participants will be assigned a random number (1 or 2), corresponding to the relevant trial arm. This will be done on the Predictiv platform when participants enter at T0. The randomisation uses a sequence of pseudo-random numbers generated using a Mersenne Twister Random Number Generator, and the numbers are automatically stored in the data on Predictiv. There will be no restrictions (eg, blocking) on the randomisation.

#### Allocation concealment and blinding

Randomisation will occur via a remote online central randomisation system via the Predictiv platform. Participants cannot access their survey data and are blinded to their group allocation. At the end of T1, we will ask participants to say which intervention arm they thought they had been allocated. The researchers will also be blinded to randomisation and group allocation, where possible.

### Data collection, management and analysis

#### Data collection and management

All data collected by BIT will be stored on BIT’s Google Drive compliant with ISO 27001,^46^ as well as the secure, password-protected Predictiv platform that only project team members can access. Personal email data collected at T1 to enable contact for the 1-month timepoint will be deleted at the end of the trial period. Data will be cleaned for test responses, duplicate hashed IP addresses (that limit the risk of individual identification), participant IDs and other unique identifiers related to the participant’s device. The cleaning code will be quality-assured by an independent researcher at BIT. Data will be sent securely to researchers at Curtin University and stored within a secure data storage drive based at Curtin University, Perth, Australia. This secure location is designed for storage of sensitive information and is the default storage option for research data generated at Curtin University. Data will be retained for a minimum of 7 years. A data management plan has been developed and approved by all partners involved in the RCT to detail data management procedures.

An attrition rate of approximately 45% between T0 and T1 is anticipated based on similar online studies.^47 48^ To promote participant retention and completion at T1, the duration from T0 to T1 is set at 7 days to give participants time to use the interventions in a timely manner and consider their hearing health needs and decision-making for the available options. We considered this time period sufficiently long to observe the intervention’s effects yet short enough to avoid significant participant attrition. The 1-month reminder email will be delivered as a behavioural ‘nudge’ in terms of intention and action to uptake hearing health. The allocated interventions will be made available to the participants throughout the trial. Interventions can be downloaded or bookmarked, and device-specific instructions will be provided to facilitate this. Additionally, the allocated intervention will be re-presented at T1, 1m and T2.

#### Confidentiality

Reidentifiable personal information will be collected and stored on password-protected secure servers at BIT and Curtin University with a two-step authentication process, restricted access to BIT and key members of the research team (MF, EB). All participants will be assigned a unique code and their de-identified data will be stored with this code. A separate document linking participant codes to their identity will be accessible only to Authors MF and EB. If requested, data will be made available to the sponsor, human ethics committee and national regulatory bodies. Confidentiality will be ensured before, during and after the trial through these measures.

#### Data monitoring

Data collection will be regularly monitored by researchers at BIT. This will include a pilot soft launch to ensure data are correctly collected and the survey is working from a technical perspective. Any required changes will be made. BIT will work with Pureprofile to monitor traffic to the survey, attrition and other issues that might arise. Any issues will be raised with the chief investigator (MF) and decisions made in consultation with the research team, as required.

Any adverse event will be immediately reported to the chief investigator, who will report the deviation to the Curtin University Human Research Ethics Office.

#### Statistical methods

A full statistical analysis plan will be finalised prior to data lock. No interim analyses to stop for efficacy or futility are planned.

Demographic and hearing characteristics of the intervention and control groups will be described at T0. For the primary and secondary outcome measures at each timepoint (T0, T1, T2), we will provide the mean and 95% CIs by group. Differences between groups will be explored at each timepoint using independent samples t-tests, with correction for Type I errors as required. The primary analysis will evaluate whether there is a difference between the intervention and control groups at the primary study endpoint T1.

Analysis of variance will be used to compare change over time on each outcome measure between the intervention and control groups. Additional analyses will be performed to explore the impact of demographic, hearing-related characteristics and intervention engagement on the outcome measures over time between groups.

Economic analysis involves estimation of societal costs and costs associated with the development and use of the decision aid, and costs of fitting hearing aids or equivalent. Additionally, the impact of the intervention of work will be explored on both employment status (focusing on hours of work per week), and measures of absenteeism and presenteeism, specifically the WHO Health and Performance Questionnaire.^42^

Acceptability and feasibility data will be summarised by descriptive statistics and compared within and between intervention groups. This will include a flow diagram of the numbers of participants across the trial as indicated in figure 1 (eg, number screened, eligible, completion at each timepoint). For the *HearChoice* group, additional analyses using website analytics on participants’ engagement with *HearChoice* across the trial period will be performed based on content viewed. These results, along with those from the evaluation outcome measures, will help inform future trials of decision aids in hearing healthcare.

After completion of all planned analyses, data will be made available on reasonable request and on signing a unilateral data sharing agreement.

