## Methods and analysis

### Trial design and setting

This is a two-arm superiority parallel RCT with an active control. The trial will compare the *HearChoice* decision support intervention to a modified Hearing Loss Option Grid originally developed in the UK based on a qualitative study^20^ and adapted for use in Australia (online supplemental appendix 1).

This article outlines the protocol (V.1.0, 20.2.25) of the *HearChoice* (RCT), which meets the Standard Protocol Items: Recommendations for Intervention Trials (SPIRIT) guidelines.^30^ The SPIRIT Checklist is shown in online supplemental file 2.

The trial was prospectively registered with the Australian New Zealand Clinical Trials Registry. This registration includes all items from the WHO Registration Data Set (V.1.3.1).^31^

The online trial will be conducted by the Behavioural Insights Team (BIT) on Predictiv, their online experiment platform. Participants will be recruited through Pureprofile, a global research panel, who will recruit participants across Australia and send them a link to the trial. All aspects of the trial (eg, informed consent, decision tool interventions and measures) will be delivered online. Participants in both arms will follow the same study schedule, with outcome measures at baseline (T0), 7 days post-intervention (T1, primary endpoint) and 3 months post-intervention (T2) (see figure 1). Participants will be paid participation fees by Pureprofile for completing each of the T0, T1 and T2 surveys. Participants will be paid the same regardless of the intervention arm to which they are allocated. The study sponsor is Curtin University, Perth, Australia, who is responsible for the conduct of the study.

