#### Sample size

We aim to recruit a sample of 640 participants at randomisation. This sample size is based on a required sample of 352 at T1 and a rate of 45% attrition between T0 and T1. This rate of attrition is typical for studies completed using the Predictiv platform.

The required sample size at T1 was calculated as necessary to detect a moderate effect size of 0.3 at 80% power and an alpha level of 0.05 in a two-tailed test. This moderate effect size was selected pragmatically as there are no published RCTs of decision aids for hearing interventions. Review of previous RCTs of patient decision aids for other, mainly chronic, conditions using the Decisional Conflict Scale revealed a wide range of reported effect sizes (0.03–3.94).^32 33^ The selected effect size of 0.3 is slightly smaller than that reported in a previous study of a similar online decision aid.^34^

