	**Effectiveness outcomes**			
Primary outcome				
Decisional conflict	Decisional conflict Scale	X	X	X
Secondary outcomes				
Readiness for hearing healthcare	Ida Institute Line 1	X	X	X
Self-efficacy for hearing healthcare	Ida Institute Line 2	X	X	X
Hearing-related quality of life	Revised Hearing Handicap Inventory—Screening	X		X
Empowerment	Empowerment Audiology Questionnaire—15 items	X	X	X
Intention to take action	Bespoke project-related question		X	X
Preparedness for decision-making	Preparation for Decision-making Scale		X	X
Impact of the decision tool	User-Mobile Application Scale—User		X	X
Action taken	Bespoke project-related question		X	X
Benefit of hearing aids	Glasgow Hearing Aid Benefit Profile Part 2			X
Economic benefit	WHO Health and Work Performance Questionnaire	X		X

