#### Primary outcome

The primary outcome, decisional conflict, is measured by the 16-item Decisional Conflict Scale.^38^ Decisional conflict is the uncertainty a person experiences when faced with a choice that involves risk, loss, regret or challenges to personal values. In this study, the choice relates to hearing healthcare. There are five subscales (Informed, Values Clarity, Support, Uncertainty, Effective Decision).

The *HearChoice* intervention will be considered effective if the estimated effect on this outcome is considered statistically significant (p<0.05) and clinically significant (Cohen’s *d*=moderate (0.3) or greater) for the overall score.

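### The T1 comparison is planned as an unadjusted t-test although the Decisional Conflict Scale is scheduled at T0: valid, but it gives up precision that baseline adjustment would provide at no extra data cost

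*Protocol article*

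**What the plan says.** The Primary outcome section states: "The primary outcome, decisional conflict, is measured by the 16-item Decisional Conflict Scale". Table 1 marks this scale at T0, T1 and T2, and Trial design and setting describes the schedule in the same way: "with outcome measures at baseline (T0), 7 days post-intervention (T1, primary endpoint) and 3 months post-intervention (T2".

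Statistical methods names one test for group differences at a timepoint: "Differences between groups will be explored at each timepoint using independent samples t-tests, with correction for Type I errors as required". The next sentence defines the primary comparison without naming a test: "The primary analysis will evaluate whether there is a difference between the intervention and control groups at the primary study endpoint T1". A separate paragraph adds: "Analysis of variance will be used to compare change over time on each outcome measure between the intervention and control groups". Further exploratory analyses cover demographic factors, hearing-related factors and engagement. The section also says that a full SAP will be finalised before data lock.

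The Sample size section gives 352 at T1 as "necessary to detect a moderate effect size of 0.3 at 80% power and an alpha level of 0.05 in a two-tailed test", and 640 randomised after 45% attrition. On allocation, Sequence generation says: "There will be no restrictions (eg, blocking) on the randomisation". The Primary outcome section calls the intervention effective only if p<0.05 and Cohen's d is 0.3 or greater on the overall score.

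**The concern.** The baseline value of the primary outcome is usually one of the strongest predictors of its follow-up value, particularly when the same instrument is repeated after seven days. The t-test does not use it. There are three consequences.

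- The standard error is larger than the scheduled data require.
- A chance difference in baseline conflict between the arms, which unrestricted randomisation allows, carries over in part into the T1 estimate. This matters more than usual here because the point estimate, and not only the p-value, decides whether the intervention is called effective.
- Testing at each timepoint includes T0. Differences between randomised arms at T0 are due to chance by design, so those tests answer no question, yet they join the set to which a Type I error correction may apply.

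**Working it through.** **Inputs from the protocol article.** d = 0.3, power 80%, two-sided alpha 0.05, 352 at T1 (176 per arm if equal), 45% attrition, 640 randomised (Sample size); success rule p<0.05 and d ≥ 0.3 (Primary outcome).

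**Assumed.** The correlation r between T0 and T1 scores is not in the document. I use 0.2 to 0.7.

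**1. The plan's own figures.** The exact noncentral-t power of an unadjusted two-sample t-test at d=0.3 is 0.7991 with 175 per arm and 0.8014 with 176. The first N to reach 80% is therefore 2 × 176 = 352, and 352 / 0.55 = 640. Both stated figures reproduce. The match also supports reading the primary comparison as that t-test.

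**2. Precision and power with adjustment.** In SD units the unadjusted standard error is √(2/176) = 0.1066. Adjusting for T0 score multiplies it by √(1 − r²). Power by normal approximation is Φ(0.3/SE − 1.96). The N of unadjusted completers giving the same precision is 352/(1 − r²).

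| r | SE of d | Power for p<0.05 at d=0.3 | Equivalent unadjusted N |
|---|---|---|---|
| unadjusted | 0.107 | 80.4% | 352 |
| 0.2 | 0.104 | 81.9% | 367 |
| 0.3 | 0.102 | 83.9% | 387 |
| 0.5 | 0.092 | 90.1% | 469 |
| 0.7 | 0.076 | 97.6% | 690 |

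**3. The joint success rule.** Unadjusted, p<0.05 is reached at an observed d of about 1.967 × 0.1066 = 0.21. The 0.3 threshold is therefore the binding condition. At a true d of 0.3 the estimate is equally likely to fall on either side of 0.3, so the rule is met about 50% of the time with or without adjustment. Away from 0.3, precision matters. The probability of an observed d ≥ 0.3 is Φ((true d − 0.3)/SE). True values of 0.4 and 0.2 are chosen here only as illustrations:

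| True d | Unadjusted | r=0.5 | r=0.7 |
|---|---|---|---|
| 0.4 | Φ(0.1/0.1066) = 83% | Φ(0.1/0.0923) = 86% | Φ(0.1/0.0761) = 91% |
| 0.2 | 17% | 14% | 9% |

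**4. Baseline imbalance.** With 176 per arm the chance T0 difference has SE 0.107 SD, so its 95% range is ±1.96 × 0.1066 = ±0.21 SD. An imbalance b shifts the unadjusted T1 difference by r × b. For b = 0.2 SD, near the edge of that range, the shift is 0.06 SD (r=0.3), 0.10 SD (r=0.5) or 0.14 SD (r=0.7). That is 20%, 33% and 47% of the 0.3 threshold.

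**5. Does the ANOVA of change do the same job?** It is listed apart from the primary analysis. If it amounts to comparing change scores, the SD becomes √(2(1 − r)), and power at d=0.3 is 66% at r=0.3, 80% at r=0.5 and 95% at r=0.7. At each value this is below the adjusted analysis (84%, 90%, 98%).

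**The case against.** **The test is inferred.** The sentence defining the primary analysis names no test, the article is a condensed document, and a SAP is to follow that could specify a covariate. This stands as a caution. Even so, the t-test is the only test named for a timepoint comparison, and 352 is exactly its sample size. The point is directed at a stated method and not at a missing detail.

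**Nothing is invalid.** This stands in full. Under randomisation the t-test's Type I error already allows for chance imbalance, and the trial has the power it claims. A reader might infer that the trial is underpowered or its primary test wrong; the reproduced 352 and 640 show otherwise.

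**The power gain overstates the benefit.** This also stands. A reader might take 80% rising to as much as 98% as the improved chance of declaring the intervention effective. It applies to the p-value alone, because the d ≥ 0.3 condition binds.

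**Imbalance and attrition.** A reader might infer that imbalance enters the estimate in full, or that adjustment repairs the 45% loss before T1. Neither is supported. Imbalance enters scaled by r. Adjustment removes only the part of attrition-related imbalance that T0 score explains, and leaves untouched any dropout that depends on unobserved T1 values. The document gives no evidence that dropout will differ by arm.

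**T0 testing is minor.** Agreed: demographic and hearing characteristics are only described, and correction is applied only where required. The outcome measures are nevertheless covered by testing at each timepoint.

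**Conclusion.** The point holds as a recommendation on efficiency and precision. On its natural reading, the primary analysis leaves a scheduled baseline measurement unused. With 176 per arm and an assumed r of 0.2 to 0.7, the cost is a standard error of 0.107 instead of 0.104–0.076, and power for p<0.05 at d=0.3 of 80% instead of 82–98%. At the low end the gain is under two percentage points; the size depends wholly on a correlation that the document does not give. At a true d of 0.3 the chance of meeting the joint success rule does not change. What improves is the reliability of the estimate on which that rule turns, with fewer wrong calls on either side of 0.3. The separate ANOVA of change does not replace adjustment in the primary test.

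**What to change.** Before the SAP is finalised:

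- Define the primary analysis as a linear model of T1 Decisional Conflict Scale total on arm, with T0 total as covariate. Report the adjusted mean difference with its 95% CI.
- Compute Cohen's d as the adjusted difference divided by the unadjusted pooled SD. Dividing by the residual SD would inflate d and change the meaning of the 0.3 criterion.
- Apply the same model at T1 and T2 to both Ida lines and empowerment, and at T2 only to hearing handicap and work performance, which Table 1 does not schedule at T1.
- Replace the between-arm tests at T0 with description.

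The cost is wording in the protocol and SAP. The T0 measurements are already scheduled, so no added data collection or participants are needed. How dropout related to T1 values is handled remains a separate question that this change does not settle.

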### Patient and public involvement

Patient and public involvement is an integral part of the research, following good practice principles.^49^ The *HearChoice* Consumer Advisory Group was involved in commenting and editing participant-focused written materials, and along with the Consumer and Community Involvement panel, contributed to the co-development of the *HearChoice* app.

## Ethics and dissemination

### Ethics

The research study has been approved by the Curtin University Human Ethics Committee HRE2023-0024. Following presentation of the online Participant Information Sheet, informed consent will be indicated online by agreeing to a series of five statements to ensure the participant has understood the project (online supplemental appendix 2). Any protocol amendments to the protocol will be submitted to the Curtin HREC for approval, and the ANZCTR clinical trial registration will be updated. Anonymised data will be made available on completion of publication of the full programme of research on signing a unilateral data sharing agreement and will be made available for 5 years.

Financial and other competing interests for the principal investigators for the trial will be documented as required.

### Dissemination

The trial and analysis will be reported according to the Consolidated Standards of Reporting Trials.^50^ Trial results will be communicated to healthcare professionals, researchers, the public, advocacy groups and other relevant groups through a combination of: international peer-reviewed publications, professional and patient advocacy publications and newsletters, blogs and social media, institutional websites of the research team, National and Health Medical Research Council and Australian Department of Health websites and bulletins, oral and poster presentations at scientific conferences and other public and wider community forums (online, in person), and a newsletter to participants interested in hearing about the results of the research. Note: all public-facing materials, whether written or verbal, will be presented in lay and accessible language with input from the project’s Community Advisory Group.

Authorship in peer-reviewed publications will be guided by the International Committee of Medical Journal Editors. Contributors who do not meet these criteria will be acknowledged in the acknowledgement sections of the paper. We do not intend to use professional writers.

## Discussion

There are major barriers to help-seeking and decision-making in hearing healthcare.^21^ These barriers lead to many adults with hearing loss not knowing how to seek help for their hearing, and not being aware of the broad range of available hearing healthcare options, leading to uncertainties as to how to make decisions about which options to choose. These barriers early in the hearing health journey result in many people living with untreated hearing loss and its consequences, such as increased risk of dementia, negative impact on ability to perform work duties, decreased opportunity for social interaction and subsequent effects on well-being.^20^,^22^ There is a paucity of validated decision tools and research to support their effectiveness, as indicated by the research priorities in Australia and the UK.^10 27 28^ The *HearChoice* research project, including this RCT, aims to address these issues by identifying the benefits of the *HearChoice* app, and its impact on the individual, including their employment. This will establish the value of *HearChoice* in terms of hearing healthcare and economic benefits. The *HearChoice* intervention will be the first comprehensive online decision support intervention co-developed for public use in Australia and evaluated with an RCT, with plans for further global reach. The *HearChoice* app will be made available online for support early in the hearing health journey, and for hearing healthcare professionals to use with clients to facilitate shared decision-making in clinics. We anticipate these benefits will result in a greater number of empowered individuals having better informed choice and control over their hearing healthcare.

There are a number of strengths and limitations to this study. This is the first RCT to evaluate the effectiveness of an online decision aid used in audiology, addressing research priorities set by key stakeholders (eg, healthcare professionals, patients).^10 27 28^ The online nature of the RCT takes a population approach that will enable Australia-wide participation and recruit participants across a wide range of hearing health journey stages. This will include those who are in the early stages of their hearing journey, who often do not present clinically (the average delay from noticing hearing difficulties to obtaining hearing aids is 8.9 years).^8^ Thus, this online trial design will help inform how the HearChoice app might be delivered and implemented in future.

The online nature of the RCT also has limitations. It may not be accessible to all demographics with hearing difficulties, in particular those who are not digitally literate and do not have access to the internet (ie, the ‘digital divide’),^51^ therefore the trial sample may not be representative of the general population. The lack of a clinical diagnosis of hearing loss (ie, by pure-tone audiometry) is a limitation, and we are reliant on self-report of hearing difficulties. However, two systematic reviews have shown that self-reported hearing difficulties are a significant factor in help-seeking behaviours and hearing aid uptake.^52 53^ The self-report of hearing difficulties may result in people over-estimating or under-estimating their hearing abilities, resulting in the RCT including some people who may not be suitable for hearing healthcare, and the inverse, whereby some people with hearing care needs who are initially approached are not identified as eligible for the trial. To address the former, further examination of the hearing difficulties will be assessed using the validated Revised Hearing Handicap Inventory-Screen^40^ and a simple baseline self-assessment of overall hearing based on a 10-point visual analogue scale (1=poor, 10=excellent).

In summary, this RCT will provide effectiveness, economic and feasibility results to guide implementation of *HearChoice* and provide valuable insights into the impact of the *HearChoice* decision aid that is designed to educate, engage and empower those with hearing difficulties.
